### Endpoints

The primary endpoint is the time to the first bowel movement. The time will be measured from the time of wound closure to the patient’s first bowel movement. Patients were advised before study participation to remember or note their first stool after surgery. A study nurse will inquire daily whether bowel movement has occurred.

The definitions of the secondary endpoints are indicated as follows. The time to tolerance of solid food is measured from the end of surgery until the patient tolerates the intake of solid food. Tolerance of food is defined as the first time the patient is able to eat solid food (any food requiring chewing) without vomiting or experiencing significant nausea within 4 h after the meal and without reversion to only enteral fluids.

Time to first flatus is the time from the end of surgery until the patient’s first flatus. The passage of flatus will be determined by questioning the patient; the passage of a bowel movement will be determined by referring to the nursing records or by the clinical judgment of the investigator or designee following questioning of the patient.

Postoperative vomiting events, determined from the nursing records, refer to the number of times the patient has to vomit.

Colonic passage time will be determined using ten radiopaque markers (Colon Transit Radiopaque Markers, P & A Mauch, 4142 Münchenstein, Switzerland, Ref: CTT6V10, CE1253). From day 1 to day 3 after surgery, the patients will receive one capsule with ten radiopaque markers to be taken at breakfast. On day 4, a single abdominal X-ray image (posterior-anterior) will be taken. The colonic passage time in hours will be calculated according to the following formula: colonic passage time = the number of markers in the colon × 2.4 [11]. The number of each radiopaque marker in the stomach, left colon, right colon, and rectosigmoid will be recorded in a 3 × 4 table. Location of the organs on the X-ray film will be done based on the gaseous outlines of the colon. If the organs are not discernible, the method described by Metcalf et al. [11] will be applied. Markers located to the right of the vertebral spinous processes above a line from the fifth lumbar vertebrae to the pelvic outlet are assigned to the right colon. Markers to the left of the vertebral spinous processes and above an imaginary line from the fifth lumbar vertebrae to the anterior superior iliac crest are assigned to the left colon. Markers inferior to a line from the pelvic brim on the right and the superior iliac crest on the left are judged to be in the rectosigmoid and rectum.

The postoperative hospital stay is the number of days from surgery until discharge. Criteria for hospital discharge include stable vital signs with no febrile morbidity for at least 24 hours, passage of stool, toleration of a regular diet, and the absence of other complications. Swiss health insurance policies and social issues sometimes require longer hospitalization than medically necessary. We will address this issue by recording the medically indicated hospitalization along with the actual hospitalization.

The time point when all the following criteria are met will be used to calculate the medically indicated length of hospitalization:Bowel movementSolid food is well toleratedNo serious pain (no opioid containing medication necessary)Unproblematic mobilizationSurgical wound without signs of inflammation or wound can be treated well in an outpatient settingDecreasing infectious/inflammatory parameters (on day 4 after surgery CRP ≤ 135 mg/l, white blood cells count ≤ 9 × 10^9^/l) [12]

Postoperative pain will be recorded three times daily using a numeric rating scale (NRS), with scores ranging from 0 (= no pain at all) to 10 (= maximal pain) in increments of 1. Additionally, the amount, type, and time of application of analgesics will be obtained from the medical and nursing records.

Postoperative mobilization will be documented for 1 week after surgery using the following categories:0: 24 h in bed1: Out of bed only to go to the bathroom2: Out of bed on free will

The overall fluid intake will be taken from the nursing records.

Blood pressure and pulse rate are recorded, usually three times daily, during the routine visits.

The postoperative intensive care unit stay is the number of days in the intensive care unit. A stay in the recovery room exceeding 24 h is counted as an intensive care unit stay.

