### Study withdrawal and stopping medication

After randomization, the patients can withdraw at any time if they own wish without giving any reason.

Study treatment will be stopped for the following reasons:Any adverse event resulting from surgery that might interfere with the study drug or might lead to meaningless endpoint data (e.g., organ failure, anastomotic failure, or postoperative dementia). Due to the complexities of postoperative morbidity, no list of fixed criteria will be established. If such an event occurs before the first study medication will be taken, the patient will be withdrawn from the study and replaced by another patient.Serious adverse events occur that are definitively or probably related to the study drug.Tachycardia, defined as a pulse of over 120/min three times within 1 hour, occurs.In the investigator’s opinion, continuation of the treatment is detrimental to the patient’s well-being.

Unless the patient wishes to withdraw from the study, all scheduled examinations will be performed as planned as long as they are meaningful and do not pose an unnecessary burden to the patient (e.g., no X-ray examination will be performed if treatment is stopped very early or if the patient has multiple vomiting events during the first 3 days postoperatively). Thus, stopping the medication does not automatically constitute withdrawal from the study.

The investigator can withdraw a study patient if a reoperation before the return to normal bowel function is required, an epidural analgesia was placed, if there are signs of renal insufficiency or an acute renal insufficiency, or if the patient clearly is not compliant (repeated refusal to take study medication or is consuming caffeine-containing beverages or food).

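### The colonic passage time formula cannot tell markers that have not yet reached the colon from markers already expelled, so the score is not monotone in the severity of bowel paralysis

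*Protocol article*

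**What the plan says.** The Endpoints section of the protocol article fixes the measurement. On dosing: "From day 1 to day 3 after surgery, the patients will receive one capsule with ten radiopaque markers to be taken at breakfast". On reading: "On day 4, a single abdominal X-ray image (posterior-anterior) will be taken". On scoring: "colonic passage time = the number of markers in the colon", multiplied by 2.4.

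On recording, "The number of each radiopaque marker in the stomach, left colon, right colon, and rectosigmoid will be recorded" in a 3 × 4 table. The stomach count is therefore kept but does not enter the formula, and the small bowel is not a recorded region.

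On localisation, the first rule is: "Location of the organs on the X-ray film will be done based on the gaseous outlines of the colon". If that fails, a published method based on bony landmarks applies. As the article describes it, its three zones are right colon, left colon, and rectosigmoid and rectum.

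The section on withdrawal and stopping medication adds, as an example of an examination that may be dropped, that "no X-ray examination will be performed if treatment is stopped very early or if the patient has multiple vomiting events" in the first three days.

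The Statistical analysis section assigns secondary continuous outcomes to a regression on mean ranks that takes account of caffeine dose, with colon transit additionally stratified by gender. Confirmatory analyses use patients with available outcome data. The article gives no rule for markers that have not reached the colon.

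**The concern.** Counting colonic markers measures colonic transit only if markers reach the colon soon after they are swallowed. This trial studies postoperative bowel paralysis. Its Background lists distention, vomiting and nasogastric decompression among the consequences, and its table reserves a column for markers in the stomach. Late arrival in the colon is thus foreseen, yet the formula treats a late marker as if it had passed.

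Because the analysis uses ranks, a low score means a fast rank. A patient whose markers are largely held above the colon can be ranked with patients who have already expelled theirs. A treatment that moves markers from the upper gut into the colon would raise the recorded passage time in such patients. The endpoint could then disagree in direction with time to first bowel movement, which it is meant to support.

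**Working it through.** **Inputs from the protocol.** Ten markers per capsule; one capsule at breakfast on days 1, 2 and 3; one film on day 4; factor 2.4 h per marker.

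**Assumptions, not in the protocol.** The film is taken at about breakfast time, so the capsules are 72, 48 and 24 h old. Each patient has one fixed upper-gut delay d and one fixed colonic time T. The values of d and T are illustrative.

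**1. The stated factor.** 24 h / 10 markers = 2.4 h per marker; equivalently 72 h / 30 markers = 2.4. The factor reproduces, and the ceiling is 30 × 2.4 = 72 h. The problem lies in which markers are counted.

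**2. Different films, same score.**
- All 30 expelled: 0 × 2.4 = 0 h. All 30 in the stomach: also 0 h.
- 10 in the colon and 20 expelled: 10 × 2.4 = 24 h. 10 in the colon and 20 above it: also 24 h.

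**3. Score against upper-gut delay.** A capsule of age a is above the colon if a < d, in the colon if d ≤ a < d + T, and expelled if a ≥ d + T. With T = 60 h:

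| Delay d | Above colon | In colon | Expelled | Score as written | All retained × 2.4 |
|---|---|---|---|---|---|
| 0 h | 0 | 20 | 10 | 48 h | 48 h |
| 20 h | 0 | 30 | 0 | 72 h | 72 h |
| 30 h | 10 | 20 | 0 | 48 h | 72 h |
| 50 h | 20 | 10 | 0 | 24 h | 72 h |
| 80 h | 30 | 0 | 0 | 0 h | 72 h |

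The score first rises, because a moderate delay keeps the oldest markers in the colon at the film. It then falls, and drops below its no-delay value of 48 h only when d exceeds 48 h.

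**4. Dependence on T.** With T = 80 h, delays of 0, 12, 30, 54 and 80 h score 72, 72, 48, 24 and 0 h, so the score is below its no-delay value once d exceeds 24 h. With T = 30 h, the same delays score 24, 24, 24, 24 and 0 h, and the score is below its no-delay value only once d exceeds 72 h. The delay needed varies with T; the loss of monotonicity does not go away.

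**5. Localisation.** Take 30 markers in the small bowel. If the colon's gas outline is visible, none is colonic, the score is 0 h, and the table has no cell for them, so they look expelled. If it is not visible, every zone of the fallback is colonic or rectal, and the score can reach 30 × 2.4 = 72 h. Similar marker distributions can thus fall at opposite ends of the scale according to bowel gas.

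**The case against.** Several objections are sound and limit the point.

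A reader might infer that the most paralysed patients will score 0 h. The documents do not support that as a general statement. It needs all 30 markers, including those about 72 h old, to lie above the colon on a film that was taken and whose colonic outline is visible. Patients with repeated vomiting may get no film, and the fallback would push the score up rather than down.

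A reader might also infer that worse upper-gut paralysis always lowers the score, or that an effective caffeine arm would look slower than placebo. The first is untrue in the illustration above, where a 20 h delay raises the score from 48 to 72 h. The second is possible, but no frequency or length of upper-gut delay after laparoscopic colectomy is given, so neither its likelihood nor its size can be estimated.

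The endpoint is named colonic passage time, and leaving stomach markers out of it fits the name. Upper-gut recovery has its own secondary endpoints, namely tolerance of solid food and vomiting. Counting all retained markers would measure a different quantity, and in the illustration it cannot separate delays of 20 h from 80 h. That argues against substituting it for the colonic endpoint.

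The stomach count is recorded, so gastric stasis can be identified afterwards. Small-bowel stasis cannot be read from the table in the same way. Rules for unreadable or missing films may stand in an analysis plan or full protocol not shown here, and their absence is not the complaint. What remains is that the formula, the table and the fallback are stated, and as stated they merge late arrival with expulsion. Omitting films after repeated vomiting reduces the number of false low scores, but it replaces them with data missing for a reason related to the outcome.

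**Conclusion.** The point holds as a measurement fault in a secondary endpoint. The formula gives the same value to markers not yet in the colon and markers already passed, and the rank analysis then treats a low value as fast transit. At the limits of the scale the discrepancy is the full 72 h; partial stasis gives a partial error. With an assumed colonic time of 60 h, the score for delays from 0 to 80 h runs 48, 72, 48, 24, 0 h. That pattern rests on fixed delays, a film near breakfast time and illustrative values of d and T.

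The algebra is certain; the practical effect on the comparison between arms is unknown. The landmark fallback is judged only as the article describes it, since its source is not available. The primary test of time to first bowel movement, the alpha levels and the sample size of 180 do not depend on this formula.

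**What to change.** 1. Add a column for small-bowel or unassignable markers to the table, and do not let a marker seen above the colon be scored as expelled. Under the landmark fallback, use the same column where the reader cannot place a marker in the colon.
2. Keep colonic passage time as the named endpoint, but flag every film with markers above the colon and state that a low colon-only value on such a film is not interpretable as fast transit.
3. Beside it, analyse the total number of retained markers, all regions × 2.4 with a ceiling of 72 h, by the rank regression already planned and with the same gender stratification.
4. Record why a film was not taken. As a sensitivity analysis, give the worst rank to patients without a film because of multiple vomiting events.

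The cost is one table column and some analysis wording; no further imaging is needed. The article reports 12 patients randomised at its status date, so on that information few films would have needed re-reading. The added measure has limits that should be stated with it: it reflects whole-gut rather than colonic transit, it saturates at 72 h, and it counts vomited markers as expelled in patients who are still filmed.

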### Study population

Study participants will be recruited from patients of the Department of General, Visceral, Endocrine and Transplantation Surgery scheduled for laparoscopic elective colon and upper rectum resection. The indication for surgery (oncologic or nononcologic) is not a selection criterion.

In particular, the patient has to fulfill the following criteria to be considered for study inclusion:The patient is scheduled for elective laparoscopic colectomy (right or left hemicolectomy, segmental resection, extended hemicolectomy, sigmoid resection, or upper rectum (anastomosis higher than 7 cm above the anal verge)).The patient’s age is equal to or over 18 years old. As long as the patient is fit for surgery, no upper age limit exists.The patient gives informed consent before surgery.

The following criteria will exclude the patients from trial participation:Participation in another concurrent interventional trialNeed for a stoma (colostomy or ileostomy) or reversal of a stoma, if the patient had complete bowel obstructionKnown hypersensitivity or allergy to caffeine/coffeeExpected lack of compliance (patient is notorious for not following medical instructions, like taking medications as prescribed, or following necessary diets)American Society of Anesthesiologists (ASA) Physical Status Score of IV or VImpaired mental state or language problemsAlcoholism or drug abusePrevious extensive abdominal surgery (any open or laparoscopic abdominal surgery except laparoscopic appendectomy, cholecystectomy, or hernia repair)Inflammatory bowel diseaseClinically significant cardiac arrhythmia (patient suffers from physical complaints or is on regular medication)Cardiac insufficiency (like the previous criterion as safe guard against the effects of caffeine)Pregnancy, lactation, or childbearing potential without using adequate contraceptionIntake of opioid analgesics, or steroids > 5 mg/day for ≥ 7 days before surgeryUnder antidepressive medicationLiver cirrhosis or compromised liver function (MELD score > 15) (Caffeine is metabolized in liver cells, and impaired liver function would result in a prolonged half-life of the caffeine.)

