To maintain the alpha level, an O’Brien Fleming alpha spending function will be used [18]. The formal significance level in the interim analysis after 60 enrolled patients is alpha = 0.0007. The alpha for the final analysis will be 0.0498 for the assessment of the time to first bowel movement in the main analysis.

For the final analysis, the superiority of caffeine over placebo for the time to first bowel movement (primary outcome) will be assessed irrespective of the caffeine dosage using a Mann-Whitney-U-statistic. Hence, the arms with 100 mg and 200 mg caffeine will be treated as one arm. To maintain the alpha level despite the interim analysis, the alpha for testing the hypothesis is 0.0498.

Secondary continuous outcomes will be assessed by regression analysis of the mean ranks considering the caffeine dosage. Colon transit time analysis will be performed while additionally stratified by gender, as colon transit time is significantly shorter in men. Categorical secondary outcomes will be assessed by logistic regression analysis considering the caffeine dosage. Final analysis will be done according to the intention-to-treat principle and compared to per-protocol analyses. Auxiliary nonconfirmatory analyses will be performed to assess the influence of baseline and treatment characteristics on the primary and secondary outcomes.

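### The fallback film-reading rule scores right-of-spine markers as right colon even where the right colon has been removed, and the transit analysis does not separate operations

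*Protocol article*

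**What the plan says.** Study population in the Protocol article lists the eligible operations as "right or left hemicolectomy, segmental resection, extended hemicolectomy, sigmoid resection, or upper rectum".

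Endpoints describes how the film is read for colonic passage time:

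- The first rule is anatomical: "Location of the organs on the X-ray film will be done based on the gaseous outlines of the colon".
- The fallback has a trigger: "If the organs are not discernible, the method described by" an earlier publication is used.
- On the right side, the fallback counts as right colon all "Markers located to the right of the vertebral spinous processes above a line from the fifth lumbar vertebrae to the pelvic outlet". No operation is exempted.
- The recording form has four sites: "The number of each radiopaque marker in the stomach, left colon, right colon, and rectosigmoid will be recorded in a 3 × 4 table". Small bowel is not among them.
- The number of markers in the colon is multiplied by 2.4 to give hours.

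Statistical analysis says that the colon transit analysis will be "additionally stratified by gender, as colon transit time is significantly shorter in men". Type of resection is not named there. Randomization and blinding describes permuted blocks and mentions no stratification by operation.

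**The concern.** The fallback map presumes an intact colon. After a right or extended right hemicolectomy, the organ to which it assigns right-of-spine markers is no longer there. A marker in that region may be in small bowel, and so not yet in the colon, or in transverse colon that remains. The rule gives both the same label, and both then count towards colonic hours.

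The form itself allows for markers upstream of the colon on day 4, since it has a stomach column. Markers still in small bowel are therefore a realistic case in a trial of bowel paralysis, and under the fallback they have no correct place to go.

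At stake is the meaning of a secondary endpoint. The same figure in hours can describe different stretches of bowel after different operations. The analysis then pools those operations, separating patients only by gender.

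**Working it through.** **1. The conversion factor.** Inputs from Endpoints: one capsule of 10 markers each morning on days 1 to 3, and one film on day 4.

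- Hours per marker = 24 h / 10 = 2.4 h, which reproduces the stated factor.
- Scale maximum = 30 markers × 2.4 h = 72 h.

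The formula is sound. The question is which markers enter the count.

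**2. Error per film.** If k small-bowel markers are counted as colonic, the excess is k × 2.4 h.

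| k | Excess |
|---|---|
| 1 | 2.4 h |
| 3 | 7.2 h |
| 5 | 12 h |
| 10 (one day's capsule) | 24 h |

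Counting a small-bowel marker as colonic can only add hours.

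**3. Average over right-resection patients.** Two further quantities are needed, and the article gives neither: the share f of films that need the fallback, and k. Both are assumed here. Mean excess = f × k × 2.4 h.

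| f | k = 3 | k = 5 | k = 10 |
|---|---|---|---|
| 10% | 0.72 h | 1.2 h | 2.4 h |
| 30% | 2.16 h | 3.6 h | 7.2 h |
| 50% | 3.6 h | 6.0 h | 12.0 h |

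**4. Chance imbalance by operation.** Of the 180 planned patients, 60 are allocated to placebo and 120 to the two caffeine arms together. For an assumed share r of right-sided resections, the SD of the difference in that share is √[r(1 − r)(1/60 + 1/120)], and the 95% range is ±1.96 SD.

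- r = 20%: SD 0.063, range ±12 percentage points.
- r = 35%: SD 0.075, range ±15 points.
- r = 50%: SD 0.079, range ±16 points.

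**5. What this could do to the arm comparison.** Multiply the edge of the imbalance range by the mean excess from step 3. The smallest combination is 0.124 × 0.72 h ≈ 0.1 h; the largest is 0.155 × 12 h ≈ 1.9 h. Either sign is possible. This covers the reading fault only, not any real difference in transit between operations.

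**The case against.** The strongest reply is that the fallback is an exception. Films are read from gas outlines first, and nothing says how often that fails. This stands, and it is why no single figure can be given for the effect.

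Second, not every right-of-spine marker after a right hemicolectomy is in small bowel, because remaining transverse colon can lie there. The rule may also misplace small-bowel markers in patients who keep their right colon. Both points stand. The narrower fault is that for some patients the label names an organ they do not have.

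Third, the article plans auxiliary analyses of baseline and treatment characteristics, and the full protocol may hold more detailed reading instructions. This stands only in part. The auxiliary analyses are nonconfirmatory, do not name the operation, and cannot re-score a marker. The article does state the fallback rule and the gender stratum, so this is more than an omission.

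A reader might infer three stronger things that the documents do not support:

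- **Biased arms.** Allocation is randomized after surgery and access to the list is restricted. The reading rule is the same in every arm.
- **An error larger than the planned effect.** Setting 24 h against the 10 h planning difference compares one patient's possible error with a difference in means on another endpoint.
- **A definite loss of precision.** Assume 40% right-sided resections, a 12 h difference between operations (8–20 h) and an SD of 20 h. The variance then rises by 0.4 × 0.6 × 12² / 20² = 8.6% (3.8–24%). As patients lost this is 1 − 1/1.086 ≈ 8% (4–19%). However, the 20 h SD is the planning value for time to first bowel movement, the other inputs are assumed, and the planned analysis uses ranks. The 12 h is also the top of the range in step 3 of the working.

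**Conclusion.** The concern holds as a minor point on a secondary endpoint. Followed as written, the fallback mislabels markers in patients without a right colon, and the planned analysis neither separates nor adjusts for the operation.

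The firm figure is 2.4 h for each small-bowel marker counted as colonic. The 0.7–12 h mean excess in right-resection patients rests on assumed ranges for fallback use (10–50% of films) and misplaced markers (3–10 per film). The true size is unknown.

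The consequences are added noise, possible chance imbalance by operation, and a measure that means different things after different resections. There is no systematic bias between arms. The primary endpoint and the sample size of 180 are unaffected.

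**What to change.** 1. In Statistical analysis, stratify the colonic passage time analysis by resection type (right-sided versus left-sided or rectosigmoid) in addition to gender. Randomization follows surgery, so the operation performed is known beforehand and is a legitimate baseline stratum.
2. In Endpoints, for right or extended right hemicolectomy films read by the fallback, record right-of-spine markers under a separate code, for example 'small bowel or remaining colon, indeterminate', instead of right colon.
3. Report colonic passage time with the indeterminate markers counted and, as a sensitivity analysis, without them. Simply dropping them would silently score them as zero hours. Genuine colonic markers would be lost and transit would look too fast, only after right-sided resections.

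The cost is one extra stratum, one extra code and one sensitivity analysis. At the status date in the article, 12 of the planned 180 patients had been randomized, so the rule could cover nearly all films; any earlier ones could be re-read.
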